### Implementation (Phase 2)

Based on the random list, after the participant has signed the informed consent form and been assessed for inclusion criteria and initial measures, they will be informed by the psychologist and lead researcher about starting the intervention or waiting on the waiting list. Those on the waiting list will be informed about their right to access the M-TBCT protocol at the end of the study if favorable results are obtained.

### Randomization and blinding (Phase 2)

Participants meeting the eligibility criteria will be randomly allocated (1:1) to M-TBCT or the waiting list. Randomization is based on a random number service (http://www.random.org, accessed on December 6, 2023), and participants meeting eligibility criteria will be informed by the psychologist and lead researcher.

### Statistical methods (Phases 1 and 2)

In Phase 1 of the study, a mixed methods approach will be employed, aligning with current recommendations for good clinical practice in feasibility analysis. These recommendations suggest that quantitative analyses should be primarily descriptive [[32], [40]]. In Phase 1, participant characteristics will be quantitatively described, while satisfaction with the program and feedback on it will be extracted from the self-report instrument and qualitatively grouped into major themes covered by the instrument. NVivo version 12 software will be used to organize and process the data.

Following the described results, an interpretative analysis and discussion of the findings will be conducted, drawing on the adopted literature. Qualitative information extracted from this instrument will also be used to explore the acceptability of the M-TBCT protocol among the target audience. An analysis predicting participant characteristics that increase or decrease adherence to M-TBCT will also be performed. According to Bowen [41], it is valid to emphasize that qualitative research methods are useful tools for understanding institutional culture.

In phase 2, categorical variables will be presented in numbers and percentages, and continuous variables will be expressed as mean values with standard deviation. Data normality will be assessed using Kolmogorov-Smirnov and Shapiro-Wilk tests. Variance homogeneity assumption will be tested with Levene's test. If the data does not meet the normality test, Bootstrapping procedures will be employed (1000 resamplings; 95 % BCa CI) to enhance result reliability, correcting for non-normal sample distribution and group size differences, and provide a 95 % confidence interval for mean differences [42].

Randomization success will be determined by no significant differences between the groups regarding demographic and clinical characteristics. Continuous variables will be analyzed using Student's *t*-test, and categorical variables will be analyzed using chi-square or Fisher's exact tests. Longitudinal data (T0, T1, and T2) for both intervention and passive control (waitlist) groups will be tracked using the repeated measures Student's *t*-test. Spearman's correlation test will assess variable correlations. M-TBCT program efficacy will be evaluated using repeated measures ANOVA to examine the main effects of time and treatment and their interaction. McNemar's test will assess changes in mental disorder risk classification after M-TBCT intervention. Effect sizes (Cohen's d) and 95 % CI will be calculated for intra- and inter-group comparisons (intervention and waitlist). The Bonferroni correction will be applied to adjust for various statistical tests.

The data will be analyzed through intention-to-treat (ITT), including all randomized participants in their initially assigned group, regardless of completing the treatment protocol. Per-protocol analysis will exclude participants with fewer than four sessions (50 % of the M-TBCT program). Attrition analysis (As-treated) will compare those who completed the protocol with those who responded only to the initial questionnaire. This study employs mixed-effects linear models (MLMs) for statistical analysis. Fixed variables, including depression, anxiety, and self-care, will be incorporated, whereas random variables will be introduced to capture intra-individual variation over time. This will enable modeling of unexplained individual differences not accounted for by the fixed variables, providing a robust approach to understanding the relationships between these variables and well-being throughout the study.

Mediation analysis will be employed to examine the potential interaction among variables, notably depression (PHQ-9), anxiety (GAD-7), cognitive distortions (CD-QUEST) and self-care (ASAS-R), and the primary outcome, represented by well-being (WHO-5). These independent variables will be assessed for their direct impact on well-being, while sociodemographic variables such as gender, age, socioeducational level, income, marital status, number of children, occupation, and working hours will be treated as covariates in the mediation analysis to control for potential confounding factors. All statistical analyses will be conducted using SPSS 28.0 software, with a significance level of 5 % for all study hypotheses.

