### Results

In Phase 1, encompassing a pilot study, the acceptability of M-TBCT will assess participants’ perceptions regarding satisfaction with the M-TBCT protocol through a self-report questionnaire. The feasibility of M-TBCT will be verified by recruitment rates (>80 %), session attendance (>60 %), and sample retention at the end of the study (>60 %).

In Phase 2, involving the efficacy of M-TBCT, the primary outcome will be assessed by the increase in well-being, measured through WHO-5. Secondary outcomes include a reduction in depression symptoms (PHQ-9), anxiety (GAD-7), cognitive distortions (CD-QUEST) and an increase in self-care capacity (ASAS-R). All scales will be administered in both groups (M-TBCT and waitlist) before the intervention (baseline assessment), at the end of the 8 sessions (final assessment), and at the 6-month follow-up. Table 2 illustrates the session and assessment flow throughout the study period.

**Table 2 tbl0002:** Session and assessment flow throughout the study period.

Study period				
	Enrollment	Allocation	Post-intervention	Follow-up
**Point in time**	Screening	Baseline	8 weeks	6 months

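### Phase 2 makes use of a BCa bootstrap depend on normality pretests and justifies it as more reliable, which it is not at this sample size; the effect on the primary outcome is small

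*Protocol article*

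**What the plan says.** The rule is in the protocol article under Statistical methods (Phases 1 and 2). For Phase 2, "Data normality will be assessed using Kolmogorov-Smirnov and Shapiro-Wilk tests". The next step is conditional: "If the data does not meet the normality test, Bootstrapping procedures will be employed". The bootstrap is specified as 1,000 resamples with a 95% BCa interval for mean differences, and its purpose is given as "to enhance result reliability, correcting for non-normal sample distribution and group size differences".

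The same section then lists the inferential methods. Student's t-tests are named, then "M-TBCT program efficacy will be evaluated using repeated measures ANOVA", and further on "This study employs mixed-effects linear models (MLMs) for statistical analysis". None of these sentences refers back to the bootstrap.

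Under Results, "the primary outcome will be assessed by the increase in well-being, measured through WHO-5". The Instruments section gives the WHO-5 raw score as 0 to 25, multiplied by 4, so the primary outcome can take only 26 values. Sample size (Phases 1 and 2) plans 72 evaluable and about 90 recruited, and allocation is 1:1.

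**The concern.** Two tests are named but the trigger refers to a single one, and nothing says which governs when they disagree. The text also does not say whether the interval stands in for a test or sits beside it. On either reading, what is reported for a mean difference can depend on a significance test of the score distribution, made after the data are seen.

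Such a gate is worth having only if the method behind it does better when the gate fires. With 36 to 45 per arm, a comparison of means does not need normal scores, and BCa intervals at this size tend to be slightly too narrow for skewed data. The rule would then move the analyst towards the more liberal procedure in exactly those cases. The stated justification, better reliability and a correction for arm sizes, would also be carried into the trial report.

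**Working it through.** **Sample size on which the check rests.** Inputs from Sample size (Phases 1 and 2): one-tailed two-sample t-test, alpha 0.05, beta 0.20, d = 0.6. The noncentrality is d × √(n/2) = 0.6 × √18 = 2.55 with 70 degrees of freedom, and power is 0.809 at n = 36 per arm. So 2 × 36 = 72, which reproduces the article's figure. With 90 randomised 1:1 there are 45 per arm at most.

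**Design of the check.** Trials were simulated with no treatment effect, comparing two arms at one visit, with 6,000 to 10,000 trials per scenario and 36/36, 45/45 or 30/42 participants. Both normality tests were run in each arm at 0.05 (Kolmogorov-Smirnov with the Lilliefors correction), and any failure counted as a trigger. These are assumptions, because the article states no test level or counting rule. It also gives no SD or distribution, so four shapes span a range:
- normal;
- WHO-5-like (rounded normal, raw mean 10, SD 4.5, limits 0-25);
- moderate skew (gamma with skewness 1, and a PHQ-9-like integer version on 0-27);
- strong skew (exponential, skewness 2).

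A separate run of the same kind at 36 per arm widens some ranges below. The Monte Carlo standard error is √(0.05 × 0.95/10,000) = 0.0022, or 0.0028 at 6,000 trials.

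**How often the gate fires and the tests disagree.**

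| Scores | At least one failure, two arms | Tests disagree, one arm |
|---|---|---|
| Normal | about 15% | about 6% |
| WHO-5-like | 28-34% | 13-14% |
| Moderate skew | 81-93% | 21-32% |
| Strong skew | about 100% | not computed |

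Cross-check at 36 per arm from single-arm failure rates: normal 1 − (1 − 0.0745)² = 0.14 against 0.149 simulated; WHO-5-like 1 − (1 − 0.168)² = 0.31 against 0.281. These are close enough for the purpose. For WHO-5-like scores most triggers come from Kolmogorov-Smirnov reacting to rounding (0.245 against 0.110 for Shapiro-Wilk).

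**Two-sided type I error at nominal 5%.**

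| Scores | t-test, no gate | BCa, 1,000 resamples |
|---|---|---|
| Normal | 5.0-5.4% | 6.1-6.4% |
| WHO-5-like | 4.8-5.4% | 5.5-6.4% |
| Moderate skew | 4.8-5.1% | 6.1-6.6% |
| Strong skew | 4.5-5.0% | 7.2-8.4% |

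**The rule as a whole, if the bootstrap replaces the test.** Error = P(pass) × error of t given pass + P(fail) × error of BCa given fail. WHO-5-like, 36 per arm: 0.719 × 0.0503 + 0.281 × 0.0652 = 0.0362 + 0.0183 = 0.0545. Over all WHO-5-like runs the range is 4.9-5.7%. Moderate skew gives 6.0-6.2%. Under strong skew the gate always fires, so the BCa figures apply.

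**Does BCa help where it is invoked?** Among trials that failed the pretest, BCa error was 5.7-8.0%, against 4.5-6.1% for the t-test on the same data.

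**Unequal arms.** At 30/42, BCa error was 6.4% (normal), 6.4% (WHO-5-like) and 7.8% (strong skew), against 5.4%, 5.3% and 4.8% for the t-test. BCa shows no correction, and the t-test showed no problem needing one.

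**The case against.** The strongest defence is that the article never says the bootstrap is used instead of anything. It may mean that a BCa interval is added to the mean-difference comparisons, and nothing ties it to the ANOVA or the mixed model. That stands. A reader might infer that the primary efficacy result itself switches between two analyses; the text does not establish this. Under the supplementary reading, though, a second interval still appears only when a pretest fails, and it can disagree with the test beside it.

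The second defence is that little is lost on the primary outcome. That also stands: the rule gives about 4.9-5.7% for WHO-5-like scores. The 7-8% figures need strong skew on an assumed unbounded shape. The article's scales are bounded, participants are selected for symptoms (SRQ-20 of 7 or more), and nothing in the article points to skew of that degree.

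Third, trigger rates depend on the counting rule. Pooling every scale, visit and arm would give higher figures, but the article prescribes no such pooling, so the figures above use two arms at one visit. Nor does chance choose the method under strong skew, where the gate fires almost every time; the problem there is undercoverage.

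Fourth, a tie-break between the tests and a random seed are details that an analysis plan may supply, and their absence is not counted here. The gate and its rationale are stated in the article, and they remain open to criticism.

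**Conclusion.** The point holds as a minor one. The article fixes a data-dependent rule that can fire on harmless data, and it defends the fallback on two grounds that fail at this sample size. BCa with 1,000 resamples was more liberal than the t-test in every scenario, by about one percentage point or less for WHO-5-like scores and by roughly three under strong skew. It did not correct for unequal arms. The t-test stayed at 4.5-5.4% throughout. The issue matters mainly for secondary scales if their scores are skewed.

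The conclusion rests on assumed distributions, a two-group mean difference at one visit, and any single failure counted as a trigger. The planned repeated measures ANOVA and mixed model were not simulated. A reader might infer a materially inflated false-positive rate for the trial's main result, or verdicts that often hang on the random seed. The documents support neither: the primary-outcome effect is small, and resampling noise matters only for results close to the significance boundary.

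**What to change.** Under Statistical methods (Phases 1 and 2):

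- Remove the normality gate. Distributional checks can stay as description.
- State which of repeated measures ANOVA and the mixed model is primary for efficacy, and analyse each outcome with it whatever the normality tests show.
- Report a BCa bootstrap interval for that same between-arm contrast, for all outcomes, as an unconditional sensitivity analysis with more resamples (for example 10,000) and a fixed seed.
- Delete the claim that bootstrapping corrects for differences in group size.

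The cost is a few changed sentences and a little more computing. No data collection or sample size is affected.

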**Methods:**

Conduct a controlled, randomized study in two phases: Phase 1 involves a pilot study to structure the M-TBCT protocol and test its acceptability and feasibility in the judiciary (*N* = 30); Phase 2, an efficacy trial with 90 participants, comparing M-TBCT to a waitlist. M-TBCT consists of 8 online, individual, weekly sessions. Participants recruited via SRQ-20, with WHO-5, PHQ-9, GAD-7, CD-QUEST and ASAS-R as outcomes.

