## Description of protocol

### Study design

This study consists of two phases. The first is a pilot study to develop the M-TBCT protocol, assessing its suitability and practicality within the judicial context. The second phase is an efficacy trial using a single-blind design with two groups: an M-TBCT intervention group and a waitlist control group. Inspired by Soler et al. [23], the first phase will involve a sample of 30 participants, divided into three blocks of 10, each receiving M-TBCT in eight weekly one-hour sessions. Participant feedback via a self-report questionnaire will guide protocol refinement.

The second phase, an efficacy trial, will have 90 participants randomly assigned to either the intervention or waitlist group, each receiving the same M-TBCT regimen. The M-TBCT protocol will be administered individually on a weekly basis, with each session lasting 1 h and totaling 8 online sessions.

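### Randomisation success is judged by non-significant baseline tests, which is not a valid criterion and cannot show balance at about 45 per arm

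*Protocol article*

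**What the plan says.** The rule is in the protocol article, Statistical methods (Phases 1 and 2): "Randomization success will be determined by no significant differences between the groups regarding demographic and clinical characteristics". The tests follow directly: Student's t-test for continuous variables, while "categorical variables will be analyzed using chi-square or Fisher's exact tests". The section does not list the variables to be tested and does not say what follows if the rule is failed.

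Two other sentences in that section bear on the error rate. All analyses are run "with a significance level of 5 % for all study hypotheses", and "The Bonferroni correction will be applied to adjust for various statistical tests", without saying which tests form the family.

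The nearest thing to a variable list has two parts. The Abstract names "WHO-5, PHQ-9, GAD-7, CD-QUEST and ASAS-R as outcomes", and Table 2 schedules all five scales at baseline. The mediation paragraph gives "gender, age, socioeducational level, income, marital status, number of children, occupation, and working hours" as examples of covariates for that analysis only.

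Under Study design, Phase 2 "will have 90 participants randomly assigned to either the intervention or waitlist group", and Randomization and blinding (Phase 2) sets the ratio at 1:1. Efficacy is evaluated by repeated measures ANOVA, with main effects of time and treatment and their interaction. Mixed models are also named, but the fixed variables given for them are depression, anxiety and self-care, not baseline WHO-5.

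**The concern.** A significance test asks whether chance can explain a difference. Under proper random allocation, chance is the explanation for every baseline difference, so rejection is always a false alarm. Non-rejection says little either, because failing to detect a difference in about 90 people is not evidence that the arms are alike. The rule can therefore err in both directions: it can label a sound randomisation a failure, and it can label arms that differ on WHO-5 a success.

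Two things are at stake. One is a wrong public statement about the validity of the trial, with no stated response to a failure. The other is false reassurance on the primary outcome's baseline value, which the efficacy analysis does not use as a covariate.

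**Working it through.** **The plan's own figure.** Sample size (Phases 1 and 2) gives 72 for a one-tailed t-test with d = 0.6, α = 0.05 and β = 0.20. The noncentral t calculation gives 36 per arm, 72 in total, with power 0.809, so the figure reproduces. The article states no error rate for the randomisation rule.

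**Inputs.** 90 randomised 1:1, taken as 45 per arm; 5% per test, assumed two-sided because the article does not say; five baseline scales; eight sociodemographic variables. Using the mediation covariates as the list for baseline testing is an assumption.

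**1. Chance of declaring failure when randomisation is sound.** For k independent tests at 5% this is 1 − 0.95^k.

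| Tests | Chance of at least one p < 0.05 |
|---|---|
| 5 | 22.6% |
| 8 | 33.7% |
| 13 | 48.7% |

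The variables will be correlated. Simulating 13 correlated variables with t-tests at 45 per arm (15,000 runs per setting) gives:

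| Correlation among scales / among demographics | Chance of failure |
|---|---|
| 0.3 / 0.1 | 47% |
| 0.5 / 0.2 | 45% |
| 0.7 / 0.3 | 40% |

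Fisher's exact test is conservative. For a binary variable at 45 per arm its actual size is about 2.6-2.7%. Four of 13 independent tests at 2.5% and nine at 5% give 1 − 0.95^9 × 0.975^4 = 43%.

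If Bonferroni covers all 13 tests, the rate is 1 − (1 − 0.05/13)^13 = 4.9%.

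**2. What a pass rules out.** The smallest observed difference, in SD units, that reaches significance is t_crit × √(2/45), with 88 degrees of freedom.

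- At 5%: 1.987 × 0.2108 = 0.42 SD.
- With Bonferroni over 13: 2.969 × 0.2108 = 0.63 SD.

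Any smaller observed WHO-5 difference passes as success. The effect the trial is designed to detect is 0.6 SD.

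**3. What an imbalance that passes does to the efficacy analysis.** Take an observed 0.3 SD WHO-5 difference at T0, and assume equal variances, no treatment effect and a baseline-to-T1 correlation of 0.5.

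- Expected difference at T1: 0.5 × 0.3 = 0.15 SD.
- Change contrast, which is the T0-to-T1 part of the interaction: 0.15 − 0.30 = −0.15 SD, against the arm with the higher baseline.
- Treatment main effect: it averages over visits including T0. If the T2 correlation is also 0.5, it carries (0.30 + 0.15 + 0.15)/3 = 0.20 SD in favour of that arm.
- Comparison adjusted for baseline: 0.15 − 0.5 × 0.3 = 0.

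**4. Precision.** In units of the outcome variance, a change score has variance 2(1 − r) and a baseline-adjusted value 1 − r². At r = 0.5 these are 1.00 and 0.75, so adjustment cuts the variance by a quarter.

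**The case against.** **The false-failure rate may be small.** The Bonferroni sentence stands in the same section as the rule, and if it covers the baseline tests the rate is about 5%. A reader might infer that sound randomisation would fail almost half the time. The article does not support that without conditions: it needs about 13 uncorrected tests, with eight variables borrowed from an illustrative list written for another analysis. This part of the objection stands. It does not rescue the rule, because the same correction raises the detectable difference to about 0.63 SD, above the design effect.

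**Baseline is already in the efficacy model.** This also stands. A reader might infer that a WHO-5 imbalance passes straight into an unadjusted post-treatment comparison and favours the better-off arm. The stated test is a repeated measures ANOVA with T0 as a response, so its interaction shifts the other way. Nor is type I error inflated: over repeated randomisations, chance imbalance is already part of the test's error rate. What remains is a shift conditional on the imbalance that occurred, and lost precision.

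**The tests could reveal subverted allocation.** The psychologist and lead researcher generates the list and tells participants their arm, so the question is reasonable. But the tests are a weak tool for it. A systematic 0.3 SD shift on one scale would be flagged 29% of the time and a 0.4 SD shift 47%; with Bonferroni over 13 tests, 7% and 15%.

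**No action follows a failure.** True: the rule produces a label, and data-driven covariate selection after a failure is a possibility, not something the article plans. A wrong label on the trial's validity is still worth removing.

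**Conclusion.** The stated rule is wrong under every reading of the section; how it fails depends on the reading. Tested at an uncorrected 5%, it risks a false verdict of failure: about 40-49% for the assumed list of 13 variables, 23-34% for five to eight independent tests. Under Bonferroni that risk falls to about 5%, but an observed difference of up to about 0.63 SD on a scale then passes. In neither case does a pass demonstrate balance.

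The effect on the efficacy result is moderate and conditional: about 0.15 SD in the change contrast for a 0.3 SD imbalance, assuming a correlation of 0.5. The article gives no correlation, so that figure illustrates the mechanism and does not predict the size. The point concerns a rule that the article states outright, so a separate statistical analysis plan would not excuse it.

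**What to change.** Delete the success criterion and the baseline t, chi-square and Fisher tests. Describe baseline characteristics by arm using counts with percentages and means with SD, which the section already plans for Phase 2.

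Prespecify that the between-group WHO-5 comparison adjusts for WHO-5 at T0, and that each secondary outcome adjusts for its own T0 value, whatever balance is observed. This removes the conditional shift shown above and leaves no choice of these covariates to be made after seeing the data.

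Dropping the tests saves work. The adjustment is a small change to the efficacy model, with T0 moving from response to covariate, so it is more than an edit of wording. No new data are needed, because Table 2 already schedules all five scales at baseline.

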### Evaluation measures

Assessments will occur pre-intervention (T0), post-intervention (T1), and at a six-month follow-up. These will include questionnaires measuring well-being (WHO-5), depression (PHQ-9), anxiety (GAD-7), reduction in cognitive distortions (CD-QUEST) and self-care (ASAS-R). Post-study, M-TBCT will be offered to the waitlist group if results are favorable. The study stages will follow the CONSORT flowchart [24] depicted in Fig. 1. The study was approved by the Research Ethics Committee of the Federal University of São Paulo (CAAE 73817423.3.0000.5505) and registered in the Brazilian Clinical Trials Registry (REBEC) 〈https://ensaiosclinicos.gov.br/〉.

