### Sample size (Phases 1 and 2)

The sample will consist of magistrates and public servants from the judiciary who score a minimum of 7 points on the recruitment instrument (SRQ-20), which is available for online completion throughout the regional jurisdiction via an electronic platform integrated into TRT5’s intranet.

The sample size for Phase 1 of the study was determined with Soler et al. [23] as a reference, considering a minimum of 30 participants. For Phase 2, the study primarily referred to a meta-analysis conducted by Khoury et al. [39], which assessed the effectiveness of 8-week mindfulness-based interventions in healthy individuals and found an average dropout rate of 10 %.

To establish statistical significance, a sample size of 72 individuals was estimated using G*Power 3.1.9.2, based on a one-tailed *t*-test for independent samples with α=0.05, β=0.20, and Cohen's *d* = 0.6. Considering an approximate dropout rate of 25 %, which is higher than that found in similar studies, an estimated recruitment of approximately 90 eligible individuals for the intervention and control groups is anticipated.

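### Efficacy is assigned to a repeated-measures ANOVA that by default keeps only complete cases, in conflict with the stated intention-to-treat analysis; no deciding term is named, and the mixed model as described does not compare the arms

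*Protocol article*

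**What the plan says.** All references are to the protocol article.

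- **Outcome and visits.** Under Results, "the primary outcome will be assessed by the increase in well-being, measured through WHO-5". Under Evaluation measures, "Assessments will occur pre-intervention (T0), post-intervention (T1), and at a six-month follow-up". That makes three values per participant, the first taken before treatment.
- **Efficacy method.** Under Statistical methods, "M-TBCT program efficacy will be evaluated using repeated measures ANOVA to examine the main effects of time and treatment and their interaction".
- **Population.** The next paragraph of that section says "The data will be analyzed through intention-to-treat (ITT), including all randomized participants in their initially assigned group, regardless of completing the treatment protocol".
- **Second model.** The same paragraph adds "This study employs mixed-effects linear models (MLMs) for statistical analysis". Its content is given as "Fixed variables, including depression, anxiety, and self-care, will be incorporated", with random terms for variation within individuals. Its purpose is given as "providing a robust approach to understanding the relationships between these variables and well-being throughout the study".
- **Expected loss.** The Sample size section reads "Considering an approximate dropout rate of 25" per cent, with about 90 to be recruited.

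The analyses are to be run in SPSS 28.0. The article gives no rule for a participant who misses one of the three assessments.

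**The concern.** The method and the population do not fit together. A standard repeated-measures ANOVA, such as the SPSS general linear model procedure, deletes every participant with a missing T0, T1 or six-month value. Someone who completes T1 but not the six-month questionnaire is lost from the T1 comparison as well. That is a completers analysis, not an analysis of everyone randomised.

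The plan also lists three effects without saying which one decides efficacy. The main effect of time can be significant when both arms improve equally. The main effect of treatment includes a baseline at which randomisation makes the expected difference zero. Only the arm-by-time interaction asks whether the arms change differently.

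The primary efficacy conclusion is at stake. Participants know their allocation and report their own outcomes, so dropout that differs by arm and by response is plausible. A complete-case result is exposed to that, and it discards T1 data already collected. With three candidate terms and a second model whose role is unclear, the basis for declaring efficacy could be chosen after the results are seen.

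**Working it through.** **1. The plan's own figure.** Inputs from Sample size: d = 0.6, one-sided α = 0.05, power 0.80, independent-samples t-test. With 36 per arm the exact noncentral-t power is 0.809, so the stated 72 reproduces. The stated 90 equals 72 × 1.25. This calculation is for a two-group t-test, not for any of the ANOVA terms.

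**2. Complete cases.** With 25% of 90 lost and nobody returning after a missed visit, 90 × 0.75 = 67.5 remain, so about 22 to 23 are excluded. This takes dropout to mean a missing questionnaire, which the article does not say.

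**3. What each ANOVA term estimates.** Take arm differences of 0, 0.6 and 0.6 SD at T0, T1 and six months (a sustained effect).
- Time: averages over arms and contains no arm comparison.
- Treatment: (0 + 0.6 + 0.6)/3 = 0.40 SD, two thirds of the post-baseline effect. If the effect halves by six months, (0 + 0.6 + 0.3)/3 = 0.30 SD.
- Interaction: compares change between arms and is not diluted in this way.

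**4. The two models side by side.** The ANOVA compares arms but needs complete records. A mixed model can use incomplete records, but the one described lists three secondary outcomes as fixed variables, lists no arm, time or arm-by-time term, and aims to relate those variables to well-being. Adding arm to that list would condition the treatment comparison on outcomes measured after randomisation. As described, neither model delivers an arm comparison in all randomised participants.

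**5. Power, as a secondary matter.** Assumptions: N = 67, two-sided 5%, equal variances and one common correlation ρ between visits. The documents give no ρ.
- Interaction: λ = N × Σ(δ/2)²/(1 − ρ), where δ is each visit's arm difference minus their mean, with 2 and 2(N − 2) df. For the sustained effect at ρ = 0.5, λ = 67 × 0.06/0.5 = 8.04, power 0.709. If the effect halves, 0.576.
- Treatment main effect: standardised difference 0.40/√((1 + 2ρ)/3) = 0.49 at ρ = 0.5, power 0.506. If the effect halves, 0.316.
- T1 contrast adjusted for baseline: 0.6/√(1 − ρ²) = 0.693 at ρ = 0.5, power 0.798.

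| ρ (sustained effect) | Interaction | Treatment main effect | Adjusted T1 contrast |
|---|---|---|---|
| 0.4 | 0.62 | 0.55 | 0.75 |
| 0.5 | 0.71 | 0.51 | 0.80 |
| 0.6 | 0.81 | 0.47 | 0.86 |
| 0.7 | 0.91 | 0.44 | 0.92 |

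**6. Attrition bias.** A simulation with six-month dropout depending on the T1 score gave complete-case estimates of the six-month change difference between 0.58 and 0.60 against a true 0.60. That is expected under a common correlation, because the change from T0 to six months is then uncorrelated with T1. It neither shows bias nor rules it out under other patterns or for the T1 contrast, so no size is claimed.

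**The case against.** The strongest replies are these.

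- **Baseline dilution.** A reader might infer that the plan averages baseline into its treatment effect as a whole. It does not: the interaction is listed too and is free of this. The dilution belongs to the main effect of treatment alone. This stands.
- **Failure of ITT.** A reader might infer that the trial will certainly not deliver an intention-to-treat analysis. The article cannot show that. A missing-data rule may sit in a fuller plan, and an ANOVA on imputed data would not be complete-case. This stands. What remains is that the stated method and the stated population conflict as written, and imputation would still not say which term decides.
- **Meaning of dropout.** The 25% may refer to sessions rather than questionnaires. Assessments are online and asynchronous, so a person who stops therapy may still respond. This stands, and makes 22 to 23 an upper figure under that reading of the 25%, not a forecast.
- **Other analyses.** The plan promises between-group Cohen's d with confidence intervals, which could use T1 responders who lack a six-month value. True, but the plan does not give it the efficacy role.
- **Power.** A reader might take the gap between 71% and 80% as the cost of losing participants. It is not. Both figures use the same 67 people; the gap reflects a different contrast and the baseline adjustment. It nearly closes at ρ = 0.7.
- **The remedy is not full ITT either.** A model of post-baseline values omits anyone who has none. If all losses occur before T1, it uses the same people as the ANOVA. This stands and is met in the fix.

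**Conclusion.** The concern holds in a limited form. The section fixes a method for efficacy that, in its standard form, cannot include all randomised participants, and the same section promises that they will be included. It lists three effects, only one of which addresses efficacy, and names no deciding term. The mixed model it mentions does not compare the arms as described.

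The size is up to about 22 to 23 of 90 excluded, if the 25% means missing questionnaires, and a treatment main effect of 0.40 SD in place of 0.60 SD if the effect is sustained. The number with a T1 value but no six-month value, which is what an all-available-data model would recover, is not given in the article. The power figures rest on an assumed correlation and are secondary to the conflict over population.

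**What to change.** Respecify the mixed model as the efficacy analysis. Promoting it as now described would not work.

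- **Outcome:** WHO-5 at T1 and at six months.
- **Fixed effects:** arm, time, arm-by-time and baseline WHO-5. Do not include depression, anxiety, self-care or other outcomes measured after randomisation.
- **Fit:** by likelihood, with within-person correlation, to every available post-baseline value.
- **Decision:** name one primary arm contrast in advance, for example T1, with the six-month contrast for H3. The article names no primary time point, so the choice is the investigators'.
- **ANOVA:** keep it as a complete-case sensitivity analysis, and do not use the main effects of time or treatment as evidence of efficacy.
- **ITT sentence:** say that the model assumes data are missing at random and omits participants with no post-baseline value, or add a sensitivity analysis that covers them.
- **Exploratory model:** if the relation of the secondary scales to well-being is still wanted, describe it separately.

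The cost is a change of wording. SPSS 28.0 fits the model and no new data are needed. The small downside is the reliance on missing at random, which does not protect against dropout that depends on unobserved response.
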